#### Measures

##### Feasibility

The primary goal of the trial is to assess the feasibility of the trial methods [73–77]. Accordingly, we will track site recruitment and retention, assess CAC characteristics that may affect implementation outcomes (e.g., team size, co-location, budget), and track team turnover, survey response rates, and missing data. Periodic reflections with key informants in each CAC (e.g., director, coordinator) will provide detailed information on the implementation process as it occurs. These structured reflections will include questions about implementation progress and completion of specific activities, barriers and facilitators to implementation, feedback on implementation strategies, and events and external influences that may impact implementation (e.g., leadership changes, new policies) [118–120]. Team members in CACs randomized to team-focused implementation will also rate the acceptability, appropriateness, and feasibility of team-focused implementation [121].

##### Team outcomes

At 0, 6, and 12 months, team members will complete an online survey assessing team interdependence, functioning, and performance. Measures are listed in Table 3. We will also assess other relevant determinants (e.g., leadership, resources, individual characteristics) [122–125]. Changes to measures may be made prior to the start of the trial to ensure an effective assessment of the hypothesized mechanisms of change for the team-focused implementation strategies developed in the Aim 1 Implementation Mapping process.

**Table 3 Tab3:** Team member survey measures

**Domain**	**Construct**	**Number of items, rating scale**
Team Member Characteristics	Age, race/ethnicity, gender Discipline, experience, tenure	7 items
Team Interdependence	Task interdependence [51]	5 items, 5-point Likert scale
	Outcome interdependence [51]	2 items, 5-point Likert scale
Affective Team Functioning	Liking [126]	4 items, 5-point Likert scale
	Psychological safety [127]	7 items, 7-point Likert scale
	Team roles and respect [126, 128]	5 items, 5-point Likert scale
Behavioral Team Functioning	Learning behavior [127]	7 items, 7-point Likert scale
	Supportive behavior [129]	4 items, 5-point Likert scale
	Communication – information exchange [130]	4 items, 5-point Likert scale
	Relational coordination [131]	7 items, 5-point Likert scale
	Conflict management [132]	5 items, 5-point Likert scale
	Reflexivity [133]	4 items, 5-point Likert scale
Cognitive Team Functioning	Clear direction [127]	3 items, 7-point Likert scale
	Shared awareness [134, 135]	6 items, 5-point Likert scale
Team Performance	Team member-rated performance [127]	5 items, 7-point Likert scale
Implementation Determinants	Implementation climate [122]	4 items, 5-point Likert scale
	Leadership engagement [122]	4 items, 5-point Likert scale
	Available resources [122]	7 items, 5-point Likert scale
Implementation Outcomes	Acceptability, appropriateness, and feasibility [121] -Of CPM-PTS -Of team-focused implementation	12 items, 5-point Likert scale

##### Implementation outcomes

Adoption and reach will be assessed with data from CPM-PTS electronic administration and CAC administrative data. Data are collected in REDCap as the CPM-PTS is administered; we will use timestamps to determine the date of the first completed screening and assess the number of completed screenings each month. CACs will provide data on the number of children served each month. Adoption will be indicated by the number of days from training to the first completed screening. Reach will be indicated by screening rates (i.e., completed screenings/eligible children) and calculated for monthly and quarterly periods. Team members will rate the acceptability, appropriateness, and feasibility of the CPM-PTS at 0, 6, and 12 months [121].

#### Statistical analyses

##### Feasibility

We will examine descriptive statistics (e.g., mean, median, range) for quantitative measures of feasibility, acceptability, and appropriateness [121]. We expect mean scores to indicate agreement that team-focused implementation is feasible, acceptable, and appropriate (i.e., scores ≥ 4 on 1–5 scale; primary hypothesis). We will evaluate data completeness and quality and look for patterns of missing data.

##### Quantitative analyses

This study is not powered to detect between-group differences. We will explore differences in team outcomes (i.e., interdependence, functioning, performance) and implementation outcomes at 6 and 12 months (exploratory hypotheses). For team outcomes, we will construct mixed effects models to estimate effect sizes and confidence intervals. We will create separate estimates and confidence intervals for each condition (i.e., team-focused implementation vs. standard implementation). Analyses will not account for the matched pairing of CACs given the low number of clusters. For implementation outcomes, we will aggregate scores for outcomes rated by team members and examine descriptive statistics (e.g., mean, range) across CACs.

##### Qualitative analyses

We will conduct thematic analysis of team member interviews using a primarily theoretical (deductive) approach [﻿^136^]. A preliminary codebook will include a priori codes for specific dimensions of team functioning (e.g., psychological safety, supportive behavior, conflict management) and implementation determinants (e.g., implementation climate, knowledge, and beliefs). Two coders will read all transcripts and refine and add codes as needed through an iterative analysis process. After finalizing the codebook, all transcripts will be independently coded by two coders and discrepancies will be resolved through consensus.

We will conduct rapid analysis of periodic reflections [﻿^117^, ^137^, ^138^]. Interviewers will take detailed notes and summarize each reflection using a spreadsheet template. The template will list multiple domains (e.g., implementation progress, challenges, suggestions for change) and provide space for key points and exemplar quotes in each domain. To enhance validity, we will ask each CAC to provide feedback on findings (i.e., member checking) [139–141].

##### Mixed methods analyses

We will integrate survey and interview data on team functioning to examine triangulation (i.e., compare results from each method; function: convergence) and elaborate on quantitative findings (i.e., deepen understanding; function: complementarity) [142, 143]. Quantitative data on implementation will be used to assess outcomes, and qualitative data from periodic reflections will be used to understand process (function: complementarity). Qualitative findings will also be used to explain quantitative findings and explore any unexpected findings (function: expansion) [142, 143]. We will integrate quantitative and qualitative data on implementation to refine team-focused implementation strategies. For example, if we identify implementation activities with low completion, we will use qualitative data to identify barriers and suggestions for improving these activities.

### Methods for Aim 2b (effectiveness aim)

#### Participants and procedures

Anonymized caregiver data will be collected continuously through an existing Outcome Measurement System [144] over an 18-month period. No caregivers or children will be enrolled in the study. At the end of their CAC visit, caregivers complete a brief anonymous survey assessing satisfaction with their experience. We will obtain post-visit survey data for caregivers served in the 6 months preceding CPM-PTS implementation and data for caregivers served in the 12 months following CPM-PTS implementation. We estimate a total sample of 288 caregivers (4 CACs*10 caregivers/month*40% response rate*18 months). We will also collect administrative data from CAC case management systems documenting referrals to mental health services and when available, data on initiation of mental health services for cases served during the 18-month study period.

#### Measures

In the post-visit survey, caregivers will rate two items assessing their understanding of their child’s mental health needs and their intention to initiate mental health services. For each child served during the study period, we will extract two dichotomous (yes/no) variables from administrative data to indicate (1) if the child was referred to mental health services and (2) if the child initiated mental health services.

#### Statistical analyses

First, we will examine data completeness and patterns of missing data for caregiver survey ratings and CAC administrative data on referrals and initiation of mental health services. We will test the effect of CPM-PTS implementation on caregivers’ understanding of mental health needs and intentions to initiate services (primary hypothesis) using multilevel linear regression models. Models will use caregiver data from all sites and include a fixed effect of pre- vs. post-implementation and a random effect of CAC to account for clustering. If model convergence becomes a problem, we will apply robust standard errors to adjust for clustering. We will also explore outcomes using an interrupted time series regression model [145, 146]. Because differences in implementation between CACs may affect our estimates of CPM-PTS effectiveness, we may conduct exploratory “dosage adjusted” analyses using weighted regression models with weights proportional to screening rates to account for differences in use of the CPM-PTS between CACs. Lastly, if there are sufficient data, we will explore changes in mental health referrals and treatment initiation after CPM-PTS implementation (exploratory hypothesis). For each CAC, we will calculate the proportion of children referred to mental health services and the proportion initiating treatment during the 6 months preceding CPM-PTS implementation and the 12 months following CPM-PTS implementation and look for changes from pre-implementation to post-implementation.

Power consideration for our primary effectiveness hypothesis (i.e., changes in caregivers’ understanding of mental health needs and intentions to initiate services) is based on testing regression coefficients in multilevel models. To detect a standardized effect size of Cohen’s *d* = 0.35 from pre-implementation to post-implementation using a two-sided *t*-test at the 5% significance level with 80% power, a “standard design” with no clustering would require 292 caregivers. We multiplied this sample size by the design effect (DE) to account for clustering. The DE is equal to (1-ICC) because the implementation predictor has zero between-cluster variation, making the multilevel design more efficient than the standard design for this aim. Incorporating the DE reduces the required sample sizes to 278 and 263 for ICCs of 0.05 and 0.10, respectively. With our estimated sample size of 288, we will achieve at least 80% power to detect small-to-medium effects (*d* = 0.35) for a range of ICCs.

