## Aim 2 methods

### Study design

The pilot trial is a cluster-randomized hybrid type 2 effectiveness-implementation study. It is designed to evaluate the feasibility of team-focused implementation and explore differences in team and implementation outcomes (Aim 2a—implementation) as well as test the effectiveness of the CPM-PTS (Aim 2b—effectiveness). Four rural CACs will implement the CPM-PTS after being randomized to either team-focused implementation (*n* = 2 CACs) or standard implementation (*n* = 2 CACs). Supplemental File 1 includes the SPIRIT checklist [110, 111], StaRI checklist [112, 113], and CONSORT checklist and flow diagram [114] for this protocol paper. The trial is registered on clinicaltrials.gov (NCT05679154).

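### The robust-standard-error fallback for the primary caregiver model cannot deliver both 5% error and the stated 80% power with four CACs

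*Protocol article*

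**What the plan says.** The number of clusters is fixed in the Study design section: "Four rural CACs will implement the CPM-PTS after being randomized". For the effectiveness aim, "Models will use caregiver data from all sites", and the models "include a fixed effect of pre- vs. post-implementation and a random effect of CAC to account for clustering". The contingency follows directly: "If model convergence becomes a problem, we will apply robust standard errors to adjust for clustering". The article does not say which form of robust standard error is meant, or which degrees of freedom or critical values go with it.

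The power paragraph in the same section is built on individual caregivers. For a standardized difference of 0.35 it states that "a “standard design” with no clustering would require 292 caregivers". The test behind that number is described as "using a two-sided *t*-test at the 5% significance level with 80% power". It then reduces the number for clustering: "The DE is equal to (1-ICC) because the implementation predictor has zero between-cluster variation". This gives 278 caregivers at an ICC of 0.05 and 263 at 0.10, against an expected 288.

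**The concern.** A cluster-robust standard error estimates variance from the spread of cluster-level contributions, and its usual justification needs many clusters. With four, the estimate rests on 3 degrees of freedom. It is biased downward unless corrected, and a critical value near 1.96 is too small. The contingency therefore swaps a model that uses individual-level information for a method that is weak in exactly this setting. In the Aim 2a quantitative analyses the article itself gives the small number of clusters as its reason for not modelling the pairing.

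At stake are the p-values and confidence intervals for both caregiver outcomes under the primary effectiveness hypothesis, if the fallback is used.

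**Working it through.** **Inputs.** Four CACs (Study design). 4 × 10 × 0.40 × 18 = 288 caregivers, with 6 months before and 12 months after implementation (Participants and procedures), so 96 pre and 192 post. d = 0.35, two-sided 5%, 80% power, ICC 0.05 and 0.10 (Statistical analyses). Equal CAC sizes (24 pre and 48 post each) are an assumption, because the article gives no sizes by CAC.

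**The article's own figures.** With 1:2 allocation, an exact noncentral t calculation gives 80.2% power at 97 + 195 = 292. Then 292 × 0.95 = 277.4 (278) and 292 × 0.90 = 262.8 (263). The stated figures reproduce.

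**False-positive rate of the fallback, balanced CACs.** Let d_g be the post-minus-pre difference in CAC g, and G = 4.
- The ordinary least squares estimate is the mean of the four d_g.
- The uncorrected cluster-robust variance is Σ(d_g − mean)²/G². The usual variance of a mean is Σ(d_g − mean)²/[G(G−1)]. The ratio is (G−1)/G = 3/4.
- With normal errors, estimate/SE therefore follows t(3) after the G/(G−1) correction, and √(4/3) × t(3) without it.

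| Standard error | Critical value | Rejection at nominal 5% |
|---|---|---|
| Uncorrected | normal, 1.96 | P(\|t3\| > 1.96 × √0.75) = 18.8% |
| Uncorrected | t(286) | 18.7% |
| Corrected | normal, 1.96 | P(\|t3\| > 1.96) = 14.5% |
| Corrected | t(286) | 14.4% |
| Uncorrected | t(3), 3.18 | 7.0% |
| Corrected | t(3), 3.18 | 5.0% |

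The ICC does not enter in the balanced case. Simulation (20,000 null datasets per scenario) agrees. With normal critical values and assumed CAC sizes of 30 to 120, rejection is 16–18% corrected and 21–22% uncorrected. With sizes of 18 to 180 it is 21–26% and 26–32%. The corrected version on t(3) gives about 5–7% under mild to moderate imbalance and 8–12% when one CAC supplies most of the data.

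**Power of the version that holds its size.** For an effect common to all CACs, the noncentrality is 0.35/[√(1−ICC) × √(1/96 + 1/192)], where √(1/96 + 1/192) = 0.125.

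| ICC | Noncentrality | Power, t(286) | Power, t(3) |
|---|---|---|---|
| 0 | 2.80 | 79.7% | 48% |
| 0.05 | 2.87 | 81.7% | 50% |
| 0.10 | 2.95 | 83.7% | 52% |

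**How often the fallback would be used.** A random-intercept model was fitted by REML in statsmodels to 600 null datasets per ICC, with balanced CACs. Non-convergence was 2.2% at ICC 0.05 and 1.7% at 0.10. Singular fits (between-CAC variance estimated at zero) were 11% and 5%. Overall rejection, with the corrected standard error and normal critical values used whenever the fit was non-converged or singular, was 7.0% and 4.7%, against 5.5% and 4.0% for the mixed model alone. Monte Carlo error is about √(0.05 × 0.95/600) = 0.9 percentage points, and convergence flags depend on the software.

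**The alternative.** CAC indicators in ordinary regression rejected in 4.7–5.2% of null datasets when the pre-post effect was common to all CACs, at every size pattern tried. Power on 288 − 5 = 283 degrees of freedom is 79.7%, 81.7% and 83.7%, unchanged to one decimal. If the effect varies between CACs (assumed SD 0.15–0.20), rejection rises to 9–19%.

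**The case against.** The strongest reply is that the article never commits to the worst variant. It says only that robust standard errors will be used, and a condensed article may leave the correction and degrees of freedom to an analysis plan that is not shown. This stands: it cannot be said that the fallback will inflate the error rate three- to fourfold, because corrected standard errors on t(3) hold about 5% with balanced CACs. But that choice brings power down to about 50%, so no analysis plan could make this fallback meet both the 5% level and the stated 80%.

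A reader might also infer that the primary effectiveness test as a whole has a 14–19% false-positive rate, or that the fallback is likely to be needed. The documents support neither. The planned analysis is the multilevel model, and the stated trigger is a convergence problem. A zero variance estimate is a boundary solution and not necessarily a convergence failure. It becomes frequent (38% of simulated datasets) only at an ICC of 0.01, which the article does not use.

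Third, CAC indicators are no cure if the pre-post effect differs between CACs, which is plausible: two CACs receive a different implementation strategy, and the article itself allows that uneven implementation could affect its estimates. This also stands, but the planned random-intercept model makes the same common-effect assumption, so on this point the replacement is no worse than the primary analysis.

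Finally, this is a pilot whose main goal is feasibility. That bears on severity. It does not make the named method suitable.

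**Conclusion.** The concern holds as a moderate issue about a conditional branch of the analysis. When the fallback is used with four CACs, it either rejects a true null about 14–19% of the time (conventional standard error, normal or individual-level critical values, balanced CACs; more if sizes are unequal) or, corrected and referred to t(3), has about 50% power at N = 288 and d = 0.35. The 80% power statement applies to neither version at a true 5% level.

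The effect on the plan's overall error rate is probably small at ICC 0.05–0.10. These figures rest on normal errors and, where stated, on equal CAC sizes and a common pre-post effect. The article gives no figures for CAC sizes or for variation in the effect.

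**What to change.** Replace the contingency sentence with: *If the random-intercept model does not converge or is singular, CAC will be entered as fixed indicator variables in ordinary linear regression.* This estimates the same within-CAC contrast on which the (1−ICC) power argument depends, needs no variance component, and makes the trigger explicit.

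Add that a cluster-robust standard error with a small-sample correction and t(3) critical values (3.18) will be reported as a sensitivity analysis, because the main model and its replacement both assume one pre-post effect across CACs. State that this analysis has only about 50% power at d = 0.35, so a non-significant result there is weak evidence of no effect.

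The cost is two sentences and three model degrees of freedom out of about 286. No additional data are needed, and there is no material loss of power under the article's own assumptions.

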### Study aims and hypotheses

Aim 1: Develop team-focused strategies to facilitate implementation in rural CACs.

Aim 2: Conduct a pilot cluster-randomized controlled effectiveness-implementation hybrid Type II trial in 4 rural CACs.

Aim 2a (implementation aim): Assess the feasibility of team-focused implementation strategies and explore between-group differences in team interdependence and functioning and implementation outcomes (i.e., days to adoption, reach, acceptability, appropriateness, feasibility).

*Hypothesis (primary)*: Team-focused implementation will be judged to be feasible, acceptable, and appropriate (scores ≥ 4 on 1-5 scale).

*Hypothesis (exploratory)*: Team interdependence and functioning will be greater in CACs randomized to team-focused implementation than comparison CACs.

*Hypothesis (exploratory)*: Implementation outcomes, including days to adoption (i.e., days from training to first use), reach (i.e., percent of children screened), and CPM-PTS acceptability, appropriateness, and feasibility, will be greater in CACs randomized to team-focused implementation than comparison CACs.

Aim 2b (effectiveness aim): Test the effect of CPM-PTS implementation on caregivers’ understanding of their child’s mental health needs and caregivers’ intentions to initiate mental health services.

*Hypothesis (primary):* Understanding of mental health needs and intentions to initiate mental health services will be greater for caregivers served after the CPM-PTS is implemented than caregivers served before the CPM-PTS is implemented.

*Hypothesis (exploratory):* Referrals to mental health services and initiation of mental health services will be greater for children served after the CPM-PTS is implemented than children served before the CPM-PTS is implemented.

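### The exploratory referral and initiation hypothesis is to be answered from separate before/after proportions in each CAC, with no combined estimate or interval planned (low severity, cheap to improve)

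*Protocol article*

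**What the plan says.** In the protocol article, *Study aims and hypotheses* gives an exploratory, directional hypothesis for Aim 2b: "Referrals to mental health services and initiation of mental health services will be greater for children served after the CPM-PTS is implemented", compared with children served before. It is worded over children served, not CAC by CAC.

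Under *Methods for Aim 2b*, *Measures* makes both outcomes binary at child level: "we will extract two dichotomous (yes/no) variables from administrative data". *Statistical analyses* then makes the analysis conditional on sufficient data, marks it again as exploratory, and gives the method: "For each CAC, we will calculate the proportion of children referred to mental health services and the proportion initiating treatment" before and after implementation, and then "look for changes from pre-implementation to post-implementation".

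Two other parts of the plan serve as comparison:
- The caregiver ratings (primary for Aim 2b) get a multilevel model over all sites.
- The team outcomes of Aim 2a are exploratory and stated not to be powered. *Quantitative analyses* nevertheless gives them mixed models with effect sizes and confidence intervals.

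**The concern.** The hypothesis concerns one change over all children served. The stated method yields four before/after pairs per outcome, eight in all, and says only that changes will be looked for. It does not say how the four CACs combine into an answer or how much of a change could be chance.

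Small rural CACs will contribute few children each, so single-site proportions will move noticeably with no effect at all. A rise in one or two CACs could be read as a signal. A real, moderate rise spread over all four could be missed, because no single CAC shows it clearly. The *Discussion* says the study will explore whether the CPM-PTS raises referral and initiation, and a reader of the results would want an estimate and its precision for that.

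**Working it through.** **Inputs**
- Four CACs and 10 caregivers per CAC per month, from "4 CACs*10 caregivers/month*40% response rate*18 months" in *Participants and procedures*. The product reproduces the planned survey sample: 4 × 10 × 0.40 × 18 = 288.
- Observation windows of 6 months before and 12 months after, from the same section.
- Children per month: not given. *Assumption:* one child per caregiver, so about 10 per CAC per month, with complete data. The 40% survey response does not apply to administrative records.
- Base rates of referral and initiation: not given. *Assumption:* 20% to 70%.
- The 10-point rise used below is illustrative. The documents set no threshold.

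The plan states no precision or power figure for these two outcomes, so there is none to reproduce.

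**Numbers of children**
- Per CAC: 6 × 10 = 60 before, 12 × 10 = 120 after.
- Four CACs: 240 before, 480 after.

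**Precision of the change**

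For one CAC with rate p, SE = √[p(1−p)(1/60 + 1/120)] = √[p(1−p) × 0.025]. With four CACs of equal size, the stratified estimate is the average of four independent differences, so its SE is half of this: √[p(1−p)(1/240 + 1/480)] = √[p(1−p) × 0.00625].

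| Rate p | SE, one CAC | 95% half-width, one CAC | 95% half-width, stratified |
|---|---|---|---|
| 20% | √0.00400 = 6.3 points | 12.4 points | 6.2 points |
| 30% or 70% | √0.00525 = 7.2 points | 14.2 points | 7.1 points |
| 50% | √0.00625 = 7.9 points | 15.5 points | 7.7 points |

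Sensitivity to volume, at a 50% rate: with 5 children per month the half-widths are 21.9 points (one CAC) and 11.0 points (stratified); with 20 per month they are 11.0 and 5.5 points.

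**Chance rises with no true change**

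400,000 simulated trials, with binomial counts out of 60 and 120 in each of four CACs:

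| Rate p | At least one CAC up by 10 points or more | At least three of four CACs up by any amount | Average of the four up by 10 points or more |
|---|---|---|---|
| 20% | 23% | 28% | 0.1% |
| 30% | 32% | 28% | 0.3% |
| 50% | 38% | 28% | 0.6% |
| 70% | 33% | 27% | 0.3% |

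A hand check at 50%: 10/7.9 = 1.26 standard errors, a one-sided tail of about 0.103 per CAC. Then 1 − (1 − 0.103)⁴ ≈ 0.35. The simulation gives 0.38 because the counts are discrete. These figures are per outcome.

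**The other direction**

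For a true rise from 50% to 60% that is the same in every CAC, two-sided power at 5% is about 25% in one CAC and 72% for the combined comparison.

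**The case against.** The strongest case against is that this is a four-CAC pilot whose primary goal is feasibility. The analysis is labelled exploratory in both places, depends on there being enough data, and drives no stated decision. The article condenses a fuller plan, and silence about intervals does not exclude them. Showing each CAC separately is also defensible: two CACs receive each implementation condition, and the protocol itself expects differences between CACs that may affect its estimates. All of this stands, and it keeps the severity low.

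It does not remove the point, because the article states a method rather than leaving one open, and that method stops short of what the same article plans for its exploratory, unpowered team outcomes. The sentence on interrupted time series does not clearly fill the gap. It names no outcomes, follows the caregiver-rating models, and comes before the separate plan for referral and initiation.

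A reader might infer more than the documents support:
- *That these outcomes cover every child, unlike the surveys.* Extraction is intended for each child served, but *Participants and procedures* collects initiation only when available, and completeness is to be examined first.
- *That they are the trial's only behavioural outcomes.* Adoption and reach under *Implementation outcomes* are also observed behaviour, taken from timestamps and administrative data.
- *That they get the weakest analysis in the plan.* Implementation outcomes in Aim 2a also get descriptive statistics only.
- *That a pooled interval would settle the hypothesis.* The comparison is an uncontrolled before/after one, and an interval does not address secular trend.

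**Conclusion.** The point holds as a low-severity improvement. The stated method gives no combined estimate and no measure of precision for a hypothesis worded over all children served, although the data are child-level and binary, so both can be computed. At about 60 children before and 120 after per CAC, reading CACs singly means uncertainty of about 12 to 16 points each way, against about 6 to 8 points for the stratified change. It also means a 23% to 38% chance per outcome that some CAC rises by 10 points or more with no effect.

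These sizes rest on the assumed volume, complete data, base rates of 20% to 70%, independence between children and, for the power figures, a common change across CACs. Incomplete initiation data would widen every interval. Effects that differ between CACs would make the pooled figure an average over these four sites only. The documents do not show that a false claim will be made; the risk is one of interpretation.

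**What to change.** If data suffice, report for each outcome:
- one CAC-stratified pre-post difference in proportions with a 95% interval, for example a Mantel-Haenszel risk difference or a binomial model with a fixed intercept per CAC;
- beside it, the four CAC-specific differences, each with its own interval;
- the number and share of children with missing data, by CAC and period.

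Keep the existing exploratory label. State that the interval is conditional on these four CACs, that effects may differ between them, and that it reflects sampling error and not secular trend.

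The cost is a few lines of analysis code and a short addition to the analysis text. It uses data already due to be extracted and changes nothing in trial conduct.
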